##### Study Settings and Participants

Eligibility screening and recruitment will be identical to procedures used for phase I. We will partner with the Centre of Excellence for Research in AIDS (CERiA) at the University of Malaya, Kuala Lumpur, Malaysia. Eligibility criteria will include the following: (1) age ≥18 years; (2) cis-gender men; (3) laboratory-confirmed HIV negative status; (4) no existing use of PrEP; (5) own a smartphone; and (6) ability to understand, read, and speak English. Participants will be discontinued from the study under any of these circumstances: (1) acquisition of HIV infection (will be referred to appropriate care); (2) participant voluntarily chooses to leave the study; and (3) the provider thinks the study is no longer in the best interest of the participant.

Participants will be recruited using both in-person and online recruitment strategies. For in-person recruitment, flyers will be given out to potential participants as well as posted at local community-based organizations. In addition, various general and MSM-specific social media and other online platforms will be chosen as venues for participant recruitment. These include placing advertisements in geosocial networking apps popular among MSM in Malaysia (eg, Grindr, Hornet) as well as posting study flyers on Malaysian MSM–focused Facebook pages. The recruitment materials will include brief information about the study and contact information (and a link to the study website) where potential participants could receive more information.

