##### Primary Outcomes

All structured interviews will be assessed online via Qualtrics (Qualtrics XM). Primary outcomes are those along the HIV prevention cascade, including uptake of HIV testing (ie, ordering of HIV self-testing kit and uploading the result via the app or HIV testing as part of the PrEP clinical care) and PrEP (ie, current use of PrEP; yes/no). Both HIV testing and PrEP uptake will be assessed at each follow-up time point (3, 6, and 9 months) using self-report and medical record review for confirmation.

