##### Analytical Plan

To test the hypothesis that the intervention group (I=JomPrEP) will be significantly more effective than the TAU group for HIV testing and PrEP uptake, we will compare the proportion for both outcomes. The null hypothesis is that the proportion of HIV testing and PrEP uptake in the intervention group and TAU is equal, expressed as follows: H_0_: p_I_=p_TAU_, where p_I_ and p_TAU_ are the proportion of HIV testing and PrEP uptake in the JomPrEP and TAU groups, respectively. Our alternative hypothesis is H_1_: p_I_>p_TAU._ We will use both intent-to-treat (ITT) and on-treatment analyses, with ITT used for efficacy. Baseline characteristics will be tested for homogeneity across the 2 groups using a *t* test or Wilcoxon rank sum test for continuous variables and chi-square test or Fisher exact test for categorical variables. Any baseline variable showing a significant difference at *P*<.05 between the 2 groups will be put into the model for adjustment. For all outcome variables assessed over a 9-month follow-up period, plots of longitudinal data over time will be provided. Prior to the primary analysis, the distribution of the missing data pattern will be examined across the 2 groups. For a subgroup of those starting PrEP, we will compare PrEP adherence using the same method and PrEP persistence using time-to-discontinuation and Cox proportional hazards ratios.

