The framework for testing the study hypotheses will compare the differences between the 2 groups (JomPrEP vs TAU) over time. To test our primary hypotheses on binary outcomes of HIV testing and PrEP uptake, a generalized linear mixed model [50] with random subject effects will be built to account for the correlation in repeated measurements within participants. Treatment assignment, time, the interaction between time and treatment assignment, and any other hypothesized confounders will be included as covariates. HIV testing and PrEP uptake proportion at the 9-month follow-up will be estimated and compared using a linear contrast statement in SAS PROC GLIMMIX. Similar analyses will be conducted for the secondary binary outcomes: optimal adherence and PrEP persistence. As an alternative analytical plan for assessing the impact of the 2 groups on adherence to PrEP, continuous adherence variables will be analyzed using a linear mixed model [50] with the same set of covariates as the binary adherence outcome and percent changes in adherence between the different assessment points will be estimated and compared between the 2 arms using the linear contrast statement in SAS PROC MIXED. For the aforementioned model, the covariance structure will be selected based on the fit statistics (eg, Akaike information criterion and the Bayesian information criterion) [51]. Given the several strategies by which PrEP adherence will be measured, we will utilize Spearman correlation coefficients and scatterplots to assess the associations between the biomedical measure (dried blood spot) [45-48] and self-report measure (Visual Analog Scale) [49].

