##### Sample Size

We calculated the sample size based on the difference we expect in the primary outcome (ie, PrEP uptake) by month 9. A sample size of 121 per group achieves 90% power to detect a 10% increase in PrEP uptake for the JomPrEP group compared with the TAU group, assuming 50% PrEP uptake in the TAU group at the 1-sided .05 significance level. A sample of 268 participants will be enrolled and randomized to the JomPrEP and TAU groups to accommodate a 10% dropout. Assuming 60% of PrEP uptake in the JomPrEP group, this sample size provides 85% power in detecting a standardized effect size of 0.5 for the secondary outcomes of adherence and persistence.

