##### Plan for Missing Data

Several strategies will be deployed to accommodate the possibility that missing data will occur. This protocol will perform both per-protocol and ITT analyses; thus, we will follow all randomized participants regardless of the treatment received [52]. Our primary analysis is valid under the assumption that missing data are missing completely at random, using the Little missing completely at random test [53]. We will evaluate the plausibility of this assumption by determining the extent and pattern of missing data and using logistic regression to identify factors associated with dropout [54]. Sensitivity analysis will be performed under the assumption of missing not at random using a selection model, pattern mixture model, or semiparametric methods [55] to examine the robustness of conclusions from the primary analysis.

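### Exit rule (3) takes a man out of the study, not only off the app, on a provider's judgement, so later primary outcomes can be lost to the 9-month ITT comparison

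*Protocol article*

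**What the plan says.** Study Settings and Participants introduces the exit rules with "Participants will be discontinued from the study under any of these circumstances". They are HIV infection, the man's own choice to leave, and, third, that "the provider thinks the study is no longer in the best interest of the participant". Only the third is at issue here.

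The other relevant statements are:

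- **Primary Outcomes:** HIV testing and current PrEP use are assessed at 3, 6 and 9 months by self-report, with record review as confirmation. "All structured interviews will be assessed online via Qualtrics".
- **Analytical Plan, analysis set:** "We will use both intent-to-treat (ITT) and on-treatment analyses, with ITT used for efficacy".
- **Analytical Plan, contrast:** "HIV testing and PrEP uptake proportion at the 9-month follow-up will be estimated and compared", from a mixed model that also takes in the earlier visits.
- **Plan for Missing Data:** "thus, we will follow all randomized participants regardless of the treatment received", and "Our primary analysis is valid under the assumption that missing data are missing completely at random". A dropout model and missing-not-at-random sensitivity analyses are also planned.
- **Sample Size:** 121 per group, raised to 268 in total "to accommodate a 10% dropout".

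**The concern.** The third rule does not separate stopping the intervention from stopping follow-up. A provider who thinks the app is unsuitable for a man has, on the wording, one course: take him out of the study. If site staff apply that as written, his later primary outcomes are not collected. An exit before month 9 removes the very value that the efficacy contrast compares.

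The reason for such an exit may also be tied to the outcome. A man judged unsuitable for PrEP would, if followed, be recorded as not using it. Taken out of the study, he becomes a missing value. Missingness that arises this way is hard to square with a primary analysis said to rest on data missing completely at random, and some of it need not occur.

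**Working it through.** **1. The texts side by side.** The exit rule ends participation in the study. The efficacy analysis is by intention to treat and looks at month 9. Plan for Missing Data undertakes to follow everyone randomized, whatever treatment they received. There are two ways to read that undertaking:

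- If it includes men removed under rule (3), it conflicts with the rule.
- If it covers only departures from treatment, there is no direct clash, but these men's later data are lost.

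On either reading, the article gives site staff no rule that keeps the outcomes coming in.

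**2. The plan's own dropout allowance.** Taking 121 per group and 268 in total from Sample Size, the allowance is 268 − 2 × 121 = 26 men. As a share, 26/268 = 9.7%, in line with the stated 10%. Each rule (3) exit uses 1/26 = 3.8% of it. How the 121 was derived is a separate matter and nothing in this step depends on it.

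**3. Effect of one exit on a crude month-9 proportion.** With 1:1 allocation, 268/2 = 134 per arm. Planned PrEP uptake is 50% (TAU) and 60% (JomPrEP).

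| Uptake | Users among 134 | Man lost is a non-user | Man lost is a user |
|---|---|---|---|
| 50% | 67 | 67/133 = 50.38% (+0.38 points) | 66/133 = 49.62% (−0.38 points) |
| 60% | 80.4 | 80.4/133 = 60.45% (+0.45 points) | 79.4/133 = 59.70% (−0.30 points) |

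If exit is unrelated to PrEP use, the expected shift is nil: at 50%, 0.5 × 0.38 − 0.5 × 0.38 = 0; at 60%, 0.4 × 0.45 − 0.6 × 0.30 = 0. These are crude proportions. The mixed model also uses any month 3 and 6 data, so its estimates would differ.

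**4. A deliberately extreme case.** Assume true uptake is 50% in both arms, that a share w of one arm exits, and that every one of those men is a non-user. The complete-case bias is b = 0.5/(1 − w) − 0.5. With 121 per arm, the one-sided error rate is 1 − Φ(1.645 − b/√(2 × 0.25/121)).

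| w (assumed) | Bias b | Error rate (nominal 5%) |
|---|---|---|
| 1% | 0.5 points | 5.9% |
| 2% | 1.0 points | 6.9% |
| 5% | 2.6 points | 10.8% |

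The values of w and the one-sided pattern of loss are assumptions; the protocol gives no exit rate.

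**The case against.** The strongest reply has four parts.

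- **The plan already follows everyone.** If the provider's decision only ends treatment, the commitment in Plan for Missing Data keeps the man in follow-up. If study contact itself is harmful, he should go under any wording. What is left is the space between those cases. This has force, and it is why the point is small. It does not remove the point, because the exit rule says the study is what ends.
- **A journal article condenses.** Arrangements for data after discontinuation may sit in the full protocol. That is fair, and their absence is not the complaint. The complaint is about a rule that is stated, and stated too broadly. If the full protocol already provides for continued follow-up, the article's sentence need only be aligned with it.
- **No consequence is shown.** The number of exits is not given, and the per-man shift in the working would hold for any lost participant, whatever the reason. Both are correct.
- **Loss is already planned for.** There is a 10% dropout allowance, a check of missing-data patterns by arm, a dropout model and missing-not-at-random analyses. These describe or bound the loss but do not recover data that could have been collected. The outreach described under Limitations is for a man who misses an assessment; it is not said to reach one who has been taken out.

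Two stronger readings are tempting. One is that the exit rule flatly contradicts the ITT plan or voids it. The documents do not support that: the follow-up commitment is framed around treatment received and stands alongside an allowance for dropout. The other is that the rule will bias the trial towards JomPrEP. Providers linked to the study may have more contact with men in the full-app arm, who have e-consults and chat with clinical staff. But nothing in the article shows that exits would differ by arm or fall mainly on non-users.

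**Conclusion.** The point holds at low severity. Followed literally, exit rule (3) stops collection of later primary outcomes and sits in conflict with following all randomized men and with ITT for efficacy. The resulting missing data are partly avoidable and may be related to the outcome.

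The size is probably small. One exit moves a crude arm proportion by 0.30 to 0.45 points, against a planned 10-point difference. The number of exits, their balance between arms and the direction of any bias are all unknown. The inflated error rates in step 4 should not be read as a forecast: they need every exit to be a non-user from a single arm, and no statement in the protocol supports that.

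The conclusion rests on taking the rule at its word, that is, on site staff treating discontinuation from the study as the end of outcome collection.

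**What to change.** Reword exit (3) alone:

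- The provider's decision ends use of the study app only.
- A provider's decision to stop PrEP is not a ground for exit. Current PrEP use is a primary outcome, so the stop is recorded as its value: not currently using PrEP.
- The month 3, 6 and 9 online questionnaires continue, with record review where available and consented, unless the man withdraws consent or study contact itself would be harmful.
- These men stay in the ITT analysis.

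The protection for the participant is kept. The cost is one clause, a matching change to the consent wording and a few extra questionnaires.

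Recovery will be partial. Self-reported PrEP use can still be collected online, but the HIV testing outcome relies in part on results uploaded through the app, which stop when app use ends. Record review is not assured either, least of all in TAU: the Results section describes a setting without an electronic health record and a clinic dashboard that serves app users at affiliated clinics.

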##### Procedures

After meeting eligibility, participants will provide written consent and complete a baseline assessment. Participants will then be randomized (1:1) to either JomPrEP or TAU. Participants in both groups will have JomPrEP installed on their phones and be guided through its use. However, participants in the TAU group will receive JomPrEP with major intervention features inactivated. They will have access to only the resources center with information on HIV testing and PrEP, mental health, and addiction support services, and the chat function to contact the research staff. The research staff will assist in downloading the app and provide a tutorial on how to use the app.

Participants in the JomPrEP group will be provided with full app access, including a customizable page (*visual representation using avatars and pseudonyms*); visual dashboard (*tracking PrEP adherence, daily mood tracker*); HIV testing plan (*ordering self-testing kits, testing site locator*); PrEP Care Plan (*PrEPxpress—HIV risk assessment, scheduling and managing appointments, e-consult, an electronic script for PrEP medicine, discrete door-to-door delivery, accessing test results*); mental health support (*screening for psychiatric and substance use disorder, referral to mental health support services*), chat function (*ability to chat with clinical and research staff*); tailored notifications (*automated reminders for follow-up care*); and resources center (*multimedia library on information and resources on HIV testing, PrEP, risks, relationships, and psychiatric and substance use disorder*). The research staff will use an onboarding checklist to orient participants to download JomPrEP and its use. Participants will be encouraged to explore and use all components of JomPrEP. Participants can earn points for completing specific tasks on JomPrEP (ie, gamification) and personalize the frequency, timing, and content for reminder notifications and follow-up PrEP services. They can also contact the research or clinical staff using the chat function for support. Anyone identified at baseline who seroconverts during the study period will be referred to appropriate HIV treatment services.

##### Primary Outcomes

All structured interviews will be assessed online via Qualtrics (Qualtrics XM). Primary outcomes are those along the HIV prevention cascade, including uptake of HIV testing (ie, ordering of HIV self-testing kit and uploading the result via the app or HIV testing as part of the PrEP clinical care) and PrEP (ie, current use of PrEP; yes/no). Both HIV testing and PrEP uptake will be assessed at each follow-up time point (3, 6, and 9 months) using self-report and medical record review for confirmation.

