## Results

As of September 2022, we have completed phase I of the proposed study. Based on a series of formative work completed during this phase, we have developed a fully functional, clinic-integrated JomPrEP app [60], which is available to download for free on both iOS and Android platforms (Multimedia Appendix 1). JomPrEP provides a virtual platform for MSM in Malaysia to facilitate their engagement in HIV prevention in a fast and convenient manner. It offers a range of HIV prevention (ie, HIV testing and PrEP) and other support services (eg, referral to mental health services), including several on-demand features (Figure 2). We have also developed a web-based “JomPrEP Clinic Dashboard,” which will provide role-based access to clinical staff from affiliated clinics to facilitate patient care for JomPrEP app users. Without an electronic health record in the local setting, our JomPrEP Clinic Dashboard functions more like an electronic health record system.

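### One of the two routes that count as HIV-testing uptake is closed to the TAU arm, so a difference favouring JomPrEP can arise even if both arms test equally often

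*Protocol article*

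**What the plan says.** Under Primary Outcomes, the protocol article gives two primary outcomes, HIV testing and PrEP uptake. Testing is spelled out in a parenthesis introduced by *ie*: "ordering of HIV self-testing kit and uploading the result via the app or HIV testing as part of the PrEP clinical care". Both outcomes are assessed at 3, 6 and 9 months "using self-report and medical record review for confirmation", with no difference by arm stated.

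Under Procedures, both arms have the app installed, but "participants in the TAU group will receive JomPrEP with major intervention features inactivated". On what TAU keeps, it says: "They will have access to only the resources center with information on HIV testing and PrEP" (and on mental health and addiction support), plus a chat with research staff. The HIV testing plan, described as "ordering self-testing kits, testing site locator", is listed under the full access given to the JomPrEP arm.

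Under Analytical Plan, the alternative hypothesis is one-sided: a higher proportion in JomPrEP than in TAU, for testing as well as for PrEP uptake. The 9-month proportions are compared by a contrast from a mixed model.

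**The concern.** A primary outcome in a randomised comparison should be attainable, and counted, in the same way in both arms. Here one qualifying route is itself a component of the intervention. In TAU the testing outcome reduces to testing done within PrEP care, which ties it closely to the other primary outcome.

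The app may also change where men test without changing whether they test. A man who would have gone to a community site and instead orders a kit in the app moves from an uncounted route to a counted one. His TAU counterpart, who still goes to the community site, stays uncounted. Testing behaviour is then equal but the measured proportions differ, in the direction of the one-sided alternative. A positive result could not be read with confidence as more HIV testing.

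**Working it through.** **Which tests qualify, by arm (definition read as written)**

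| Where the test happens | JomPrEP | TAU |
|---|---|---|
| Kit ordered and result uploaded in the app | counts | not available |
| Within PrEP clinical care | counts | counts |
| Community site, hospital, non-PrEP clinic, bought kit | does not count | does not count |

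The first row follows from setting "ordering of HIV self-testing kit and uploading the result via the app" beside the list of features TAU retains. The second follows from "or HIV testing as part of the PrEP clinical care", which is not an app function. The third row matters because tests in that row can make up a different share of testing in the two arms.

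**Inputs**

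- 121 per group and one-sided .05: Sample Size section.
- T, the true proportion tested, equal in both arms: assumed, as the article gives no testing rate.
- u and v, the shares of testers in TAU and JomPrEP who test only by routes that do not qualify: assumed.

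The article has no figure for the testing outcome to reproduce. Its 121 per group was set for PrEP uptake and is used here only as the available sample size. Whether it is adequate for PrEP uptake is a separate question, and nothing here depends on it.

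**Formulas**

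Measured JomPrEP proportion p_I = T(1 − v). Measured TAU proportion p_T = T(1 − u). Artefact = p_I − p_T = T(u − v).

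Chance of rejection with a pooled-variance z test:

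Φ{[(p_I − p_T) − 1.645 × se0] / se1}

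where p̄ = (p_I + p_T)/2, se0 = √[2p̄(1 − p̄)/121] and se1 = √{[p_I(1 − p_I) + p_T(1 − p_T)]/121}.

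**One case in full: T = 50%, u = 20%, v = 0**

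- p_I = 0.50, p_T = 0.40, p̄ = 0.45.
- se0 = √(0.495/121) = 0.0640; se1 = √(0.490/121) = 0.0636.
- (0.10 − 1.645 × 0.0640)/0.0636 = −0.08, so the chance of rejection is 46.7%.

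**Range at T = 50%**

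| u | v | JomPrEP measured | TAU measured | Artefact (points) | Chance of rejection |
|---|---|---|---|---|---|
| 0% | 0% | 50% | 50% | 0 | 5.0% |
| 10% | 0% | 50% | 45% | 5 | 19.3% |
| 20% | 0% | 50% | 40% | 10 | 46.7% |
| 30% | 0% | 50% | 35% | 15 | 76.5% |
| 50% | 0% | 50% | 25% | 25 | 99.3% |
| 30% | 10% | 45% | 35% | 10 | 47.7% |
| 50% | 25% | 37.5% | 25% | 12.5 | 67.6% |
| 50% | 50% | 25% | 25% | 0 | 5.0% |

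With u = 20% and v = 0, the result is 8 points and 36.3% at T = 40%, and 12 points and 59.1% at T = 60%.

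The z test stands in for the planned mixed-model contrast at month 9. The artefact T(u − v) comes from the definition, not from the choice of test.

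**The case against.** The strongest case against the point is that ascertainment is common to both arms. The article plans self-report with record review and states no difference by arm, and the questionnaires in Table 1 are not restricted to one arm. The information for an arm-neutral outcome may therefore already be collected. The parenthesis also stands in a condensed article and is not a scoring rule. This stands in part. It makes repair easier, but it describes how the outcome is found out, not what qualifies. A TAU participant who truthfully reports a community-site test still meets neither route.

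Second, JomPrEP tests can go uncounted too. The site locator in that arm points users to testing sites, and a test taken there outside PrEP care fails the same definition. This stands in full and is why v is in the formula.

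Third, only one of the two primary outcomes is affected. The sample size rests on PrEP uptake, which is defined without reference to the app. That also stands.

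Three stronger readings are tempting but unsupported:

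- A reader might infer that the outcome consists only of app functions that TAU lacks, so that a difference must arise. Testing within PrEP care is open to TAU, and the artefact is zero when u = v.
- A reader might equate TAU testing with the planned 50% PrEP uptake and deduce a fixed gap. PrEP uptake is defined as current use, so a man tested in PrEP care who never started or later stopped counts for testing but not for uptake. Any such gap also needs an assumed testing rate.
- A reader might infer uneven confirmation from the Results section: "Without an electronic health record in the local setting, our JomPrEP Clinic Dashboard functions more like an electronic health record system". That sentence reports the lack of an electronic record, not of medical records, and record review is planned without distinction by arm.

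**Conclusion.** The definition is wrong as written for a two-arm comparison: one of its two qualifying routes exists only in the JomPrEP arm, and TAU tests outside PrEP care do not qualify. A spurious difference can therefore arise under equal testing, and it favours JomPrEP whenever u exceeds v. Its size cannot be fixed from the article. Over the values tried at T = 50%, it runs from 0 to 25 points, with a chance of rejection from the nominal 5% up to 99.3%; allowing a quarter of JomPrEP testers to go uncounted against half in TAU still gives 67.6%. These figures rest on the assumed T, u and v, on reading the *ie* list as closed, and on a simple two-proportion test with 121 per group. They show how sensitive the result is and are not estimates of what the trial will find.

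The point deserves correction because it concerns a primary outcome. It also cannot be fully repaired afterwards if tests from other sources were not recorded alike in both arms.

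**What to change.** Define the primary testing outcome identically in both arms: at least one HIV test from any source (self-test however obtained, community site, clinic, hospital or PrEP care) in the follow-up interval. Use the same questionnaire item and the same confirmation procedure in both arms. Report app-ordered kits with uploaded results as a process measure in the JomPrEP arm.

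The questionnaires at 3, 6 and 9 months and the chat with research staff already exist in both arms, so little new data collection is needed. The cost is still more than a change of wording. The outcome definition in an approved and registered protocol must be amended, and confirming tests from varied sources takes some staff effort. The observed effect on testing may also be smaller, because the part due to the definition is removed.
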